## Abstract

**Background:**

Given the aging population worldwide and the COVID-19 pandemic, which has been found to be associated with a deterioration in Alzheimer’s disease (AD) symptoms, investigating methods to prevent or delay cognitive decline in preclinical AD and AD itself is important. The trial described in this protocol aims to evaluate the effects of a staged integral art-based cognitive intervention (SIACI) in older adults with CIs (preclinical AD [SCD or MCI] and mild AD), in order to gather evidence on the effects of SIACI on cognition and psychological/psychosocial health gains and determine the mechanisms.

**Methods:**

The planned study is a single-center, parallel-arm, randomized controlled trial with allocation concealment and outcome assessor blinding. A total of 88 participants will be randomized to two groups: (i) an intervention group that receives the 16-week, 24-session SIACI program and (ii) a waitlist control group (which will receive the SIACI program after completing the follow-up assessment). Global cognitive function, specific domains of cognition (memory, language, executive function, and visuospatial skills), and other health-related outcomes (quality of life, anxiety, depression, sleep quality, and physical activity level) will be measured at baseline, immediately after the intervention, and at the 6-month follow-up. Blood biomarkers, event-related potential (ERP)-P300, and magnetic resonance imaging (MRI) data will be collected at baseline and immediately after the intervention to explore the mechanisms of SIACI.

**Discussion:**

The trial will elucidate the immediate and long-term effects of SIACI based on neuropsychological testing and blood biomarkers, and neuroscience involving ERP-P300 and MRI parameters will make it possible to explore the mechanisms of SIACI in older adults with CIs. The results will provide evidence on the effectiveness of an AT-based cognitive intervention, which may delay or even halt cognitive decline in preclinical AD and AD itself.

**Trial registration:**

ChiCTR, ChiCTR2100044959. Registered 03 April 2021.

**Supplementary Information:**

The online version contains supplementary material available at 10.1186/s12877-022-02961-4.

## Background

Dementia and cognitive impairments (CIs) are some of the most significant issues for ageing populations, and they are becoming increasingly hard to ignore. With an ageing population, China has 264 million people aged ≥60 years [1]. Around 10–11 million people aged ≥60 years in China have dementia, and > 60% of patients with dementia have Alzheimer’s disease (AD) [2]. Additionally, there are approximately 31 million individuals in China with mild cognitive impairment (MCI) [2]. In total, China has approximately 50 million patients with CIs, but most of them are not diagnosed or treated. Social isolation or disengagement due to the COVID-19 pandemic has been found to be associated with a deterioration in AD symptoms and increased symptoms of anxiety and depression, and the pandemic is thought to have accelerated cognitive decline in ageing populations [3]. We speculate that the prevalence of CIs will substantially increase as the population continues to age, and this patient population will have a large effect on society. Along with improvements in health consciousness among people in China, there is a growing concern specifically about brain health and AD, which has prompted more individuals with self-reported cognitive decline to seek medical advice [4].

AD, the most common form of dementia, is a slow, but progressive and irreversible, progressive neurodegenerative disorder resulting in a loss of abstract thinking, memory, language, orientation, and ultimately impaired daily functioning that leads to loss of independence [5]. MCI is a syndrome characterized by mild cognitive decline in one or more domains (such as memory, language, attention, visuospatial skills, information processing speed, and executive function), but remain largely intact and independence is preserved [6]. Subjective cognitive decline (SCD) occurs when individuals experience a subjective decrease in cognitive function, but cognitive performance based on neuropsychological testing and daily functioning shows no evidence of objective CIs, and biomarkers of preclinical AD (such as amyloid-β [Aβ] deposition and grey matter volume loss) are not present [4]. MCI and SCD are currently generally considered to represent preclinical AD [7]. Almost 50% of cases of preclinical AD will progress to dementia, and approximately 60% of affected individuals are estimated to progress to AD, highlighting the importance of early intervention for CIs [8, 9]. The emergence of COVID-19 highlights the need for large efforts to develop new technologies and other interventions to improve the prevention, treatment, and management of CIs, as small COVID-19 outbreaks could arise at any time in any population, requiring social isolation.

Notably, in individuals with AD-related CIs (who have impaired memory, language, and reasoning), the frequent concomitant emergence of depression, anxiety, and personality changes may further erode quality of life [10, 11]. For individuals with preclinical AD or AD itself, a targeted, holistic intervention may preserve both cognition and psychological/psychosocial health. More specifically, it may slow the cognitive decline by capitalizing on the existing cognitive reserve to deliver direct skill training and/or training regarding compensatory, affective, and/or social strategies that may increase brain plasticity in CIs, potentially even restoring normal ageing [12, 13]. As there is a substantial body of evidence on the role of cognitive reserve in shaping AD onset and progression, more attention has been directed to non-pharmacological therapeutic interventions. These interventions are designed to improve cognitive engagement among older adults, and they may alleviate cognitive decline and improve psychosocial aspects of AD-related MCI and AD itself without significant adverse effects [14]. In particular, art therapy (AT) has been developed as a strategy to preserve the cognition and psychological/psychosocial health of older adults, decreasing the progression of dementia even in the preclinical stage [15, 16].

AT is a form of psychotherapy that involves using art-making activities to enhance physical and mental health, which can be tailored to meet a range of needs for different individuals [17]. Art-making activities include performance arts (music, drama, and dance), visual arts (painting, collage, knitting, sculpture, and pottery), literary arts (novel-writing, poetry, and other text-related activities), and the huge range of applied arts (art design, architectural design, and industrial art). AT is thought to be effective because of its biological and humanistic mechanisms. Biologically, AT can engage participants in several cognitive processes, such as planning, creativity, verbal expression, decision-making, cognitive control, and abstract thinking, which may provoke plasticity in the neural pathways that mediate creative cognition and perceptuomotor integration [18–20]. As for the humanistic mechanism, AT is related to person-centered theory [21], and it can offer the opportunity for self-expression, social interaction, and emotional relief in a failure-free environment, which promotes psychosocial wellbeing [22–24]. Seifert et al. [25] reported that for individuals with dementia, AT-based interventions improved mental state, concentration, corporeal memory, self-esteem, self-reliance, and physical activity. Mahendran et al. [26] found that older adults with MCI who received AT had better outcomes than those who received usual care, with significant improvements in memory, attention, visuospatial skills, and executive function at 3 months and sustained improvements in memory at 9 months. Additionally, functional magnetic resonance imaging (fMRI) of retired adults who participated in weekly visual art creation indicated that there was improved brain region interactions (particularly between the frontal, posterior, and temporal brain regions), suggesting that art creation could be an important tool to prevent cognitive decline in older adults [20]. Collectively, these studies contribute to the limited literature on the effects of AT on cognition and psychological/psychosocial health in older adults, and they provide evidence that AT induces plasticity in neural pathways that mediate creative cognition and perceptuomotor integration.

Although no curative pharmacotherapy currently exists for AD, a growing number of studies have documented the significant benefits of AT [15]. AT can be adapted to fit the needs of individuals in the earliest stages of SCD to the later stages of severe CIs [27]. Recently, a based on current evidence, no AT type was significantly more effective in dementia patients than the other types [28]. Additionally, the meta-analysis found that studies on a combination of visual art, music, and drama interventions found significant improvements in at least one outcome measure, such as mental stimulation, verbalization, personal control, positive emotional reactions, satisfaction, and self-esteem [28]. This suggests that a combination of therapy types that engage participants in a variety of art activities may be effective for combating cognitive decline. Moreover, for some individuals, ongoing therapy involving only a single type of art may be difficult (due to issues related to the art form, the media used, and/or the individual’s personality characteristics). However, due to the complex mechanisms of AD and the limited research on combination AT, little is known about combination AT.

To these ends, we aim to conduct a methodologically rigorous randomized controlled trial (RCT) to evaluate the effects of a SIACI program on neuropsychological outcomes in older adults with CIs (preclinical AD [SCD or MCI] and mild AD), in order to gather evidence on the effects of SIACI on cognition and psychological/psychosocial health gains and to determine the mechanisms of SIACI. As most related studies have reported improvements in memory, executive function, or other cognitive domains (based on neuropsychological assessment) [16, 29–32], we plan to investigate the changes in these domains between baseline and after the SIACI. In particular, the participants’ functional brain activity during visuospatial working memory and executive tasks will be assessed by magnetic resonance imaging (MRI) in order to determine whether cognitive improvements in SIACI participants are associated with alterations in functional brain activation (which may underlie potential compensatory mechanisms that improve cognitive performance). In addition, effective interventions modify changes that are known to occur in neurodegenerative diseases (like AD), such as changes in neuroprotective growth factors (e.g., brain-derived neurotrophic factor [BDNF]) [33], inflammatory factors (e.g., interleukin [IL]-6 and tumor necrosis factor [TNF]-α) [34, 35], AD-related pathological biomarkers (e.g., Aβ and phosphorylated tau) [36, 37], cognition-related electrophysiological effects (e.g., event-related potential [ERP]-P300) [38], and reduced neurocognitive functions. We hypothesized that the 16-week, 24-session SIACI will effectively improve neurocognitive performance in older adults with CIs, potentially via divergent molecules (e.g., BDNF, IL-6, TNF-α, Aβ-42, Aβ-40, and phosphorylated and total tau) and neural pathways.

## Methods

### Study aim, design, setting, and ethics

To evaluate the effectiveness and explore the mechanisms of a SIACI regarding preventing or delaying cognitive decline in older adults, a single-center, parallel-arm RCT will be conducted, with allocation concealment and outcome assessor blinding (Fig. 1).

**Fig. 1 Fig1:**
[figure not shown]
SIACI study flowchart

A total of 88 eligible participants will be randomized to the 16-week, 24-session SIACI group and 16-week waitlist control group. This study will take place at Fujian Provincial Hospital, which is the largest tertiary grade A comprehensive hospital in Fujian Province, China. It is affiliated with the Fujian Provincial Medical Geriatrics Centre, Image Quality Control Centre, and Clinical Laboratory Centre. It is also the largest Public Experiment Service Platform, with highly developed support and laboratory facilities. Data collection for the trial is expected to be completed by late 2023.

As the study involved the older adults with CIs, a few specific ethical procedures were followed and ensured. Only those who signed the consent form would be included in this study, and a guardian as the legal representative was asked to co-sign the consent form. All procedures will be conducted according to the Declaration of Helsinki. The trial has been registered in the Chinese Clinical Trials Registry (ref. ChiCTR2100044959).

### Participants

#### Recruitment and screening

Eighty-eight participants are currently being recruited for the 16-week trial. There are multiple challenges associated with recruiting older adults with CIs into nonpharmacological trials, including stringent medical eligibility criteria, issues ensuring sample representativeness, and the time and effort required of participants that impact motivation to enroll. Thus, to ensure successful and timely enrollment, we are using proactive recruitment strategies, including memory clinic referrals, searches of electronic health follow-up records of the hospital, community outreach (communities, which are near the study hospital, using posters, leaflets and brochures, educational presentations, and a recruiting stations), and media outreach (e.g., local newspapers and online media have published our previous work on the potential benefits of a visual art-based intervention for brain health in MCI patients). If there is restricted site access among the participants during the study because of COVID-19, the time window between baseline and follow-up assessments will be increased to approximately 2–4 weeks.

Potential participants who respond to the recruitment strategies and contact the researchers will be carefully screened for study eligibility at an in-person visit. Participants who meet the inclusion and exclusion criteria will be enrolled, receive information about the trial, and have a discussion with the clinical research coordinator regarding this information. Those who are willing to participate will undergo baseline assessment.

#### Diagnostic criteria

MCI will be diagnosed based on the Peterson diagnostic criteria of MCI [39], as follows: (1) self-reported memory problems, preferably confirmed by someone close to the participant; (2) memory impairment in accordance with age and education (Montreal Cognitive Assessment [MoCA] [40] score of 13–14 for individuals with no formal education, 19–20 for those with 1–6 years of education, and 24–25 for those with ≥7 years of education); (3) intact activities of daily living (ADL) [41, 42] (ADL score < 25 for age ≥ 75 and < 23 for age < 75); and (4) absence of dementia (Mini-Mental State Examination [MMSE] [43] score of 24–30).

SCD will be diagnosed based on the two major features described by the working group of the Subjective Cognitive Decline Initiative (SCD-I) [44], as follows: (1) a self-experienced persistent decline in cognitive capacity (compared to a previously normal cognitive status), which is unrelated to an acute event, and (2) normal performance on standardized cognitive tests used to classify MCI, adjusted for age, sex, and education.

AD will be diagnosed based on the National Institute of Neurological and Communicative Disorders and Stroke-Alzheimer Disease and Related Disorders Association (NINCDS-ADRDA) diagnostic criteria for probable AD [45], and the presence of mild AD will be determined based on an MMSE score of 21–26.

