#### Sample size determination

The required sample size was estimated using PASS v11.0 (NCSS, Kaysville, UT, USA) based on a completely random design for comparing the means of two independent samples. To our knowledge, there is no previous study on a comprehensive intervention for CIs among older adults in mainland China, so we estimated the effect size of one of the primary outcomes (general cognitive function) based on our previous study that used creative expression therapy to improve MCI patients’ cognitive function [46] . The study was like the planned trial in some respects, as both are RCTs, one of the primary outcomes is general cognitive function, and one of the primary outcome measurement tools (MoCA) is the same. Our previous study [46] found MoCA scores of 24.68 ± 1.84 and 23.13 ± 1.68 in the intervention and control groups, respectively. A sample size of 35 participants per group was determined to be sufficient to detect an effect with a type 1 error rate of 5% (α = 0.05) and 95% power (β = 0.05). Taking into consideration a 20% attrition rate, a total of 88 participants will be needed, with 44 participants per group.

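### Closed two-score MoCA ranges for MCI leave more impaired people without dementia in no entry category, and MMSE 24–26 counts towards both no dementia and mild AD with no stated precedence

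*Protocol article*

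**What the plan says.** All of the rules stand in the Diagnostic criteria section of the protocol article.

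- **MCI.** Four items are needed: a memory complaint, memory impairment on the MoCA, intact ADL, and no dementia. The MoCA item asks for a "score of 13–14 for individuals with no formal education", then "19–20 for those with 1–6 years of education, and 24–25 for those with ≥7 years of education". The ADL item is written as one-sided limits: "ADL score < 25 for age ≥ 75 and < 23 for age < 75". Absence of dementia is given as MMSE 24–30.
- **SCD.** Besides a self-experienced decline, it requires "normal performance on standardized cognitive tests used to classify MCI, adjusted for age, sex, and education".
- **Mild AD.** AD is diagnosed by the NINCDS-ADRDA "diagnostic criteria for probable AD", and then "the presence of mild AD will be determined based on an MMSE score of 21–26".

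The Inclusion criteria section admits only people who have one of these three diagnoses. No text says which diagnosis prevails at MMSE 24–26.

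The Sample size determination section reports MoCA values from the sponsor's earlier trial in MCI patients: 24.68 ± 1.84 and 23.13 ± 1.68 "in the intervention and control groups, respectively".

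**The concern.** The MCI memory item has a floor as well as a ceiling. A floor is odd for an impairment criterion, because it shuts out people for being more impaired while they are still free of dementia. Such people cannot enter through SCD, which needs normal results on the same tests, or through mild AD, which needs probable AD. They drop out of a trial that presents itself as covering several stages of AD.

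The MMSE ranges raise a second, smaller matter. The number that stands for absence of dementia in the MCI rule overlaps the number that stands for mild AD, and the Background calls AD a form of dementia.

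What is at stake is who enters and under which label. Recruitment is already under way. The MoCA is also a primary outcome and the variable used for sizing, so the entry rule shapes the baseline range of that outcome. If the screening staff apply an unwritten cut-off instead, the people enrolled differ from those the published criteria describe.

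**Working it through.** **1. The plan's own figure.** The sample size is reproduced first, to confirm the MoCA inputs.

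- Difference: 24.68 − 23.13 = 1.55.
- Pooled SD: √((1.84² + 1.68²)/2) = √3.104 = 1.762.
- Normal formula, two-sided α = 0.05, 95% power: n = 2 × (1.960 + 1.645)² × 3.104 / 1.55² ≈ 33.6, so 34 per group. The t-test version gives 34.6, so 35.
- Attrition: 35 / 0.80 = 43.75, so 44 per group and 88 in total.

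The stated 35, 44 and 88 are reproduced. This point does not alter them.

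**2. The gap.** Take a person with at least 7 years of education, a memory complaint, intact ADL, MMSE 26, no dementia and MoCA 22.

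| Category | Requirement | Met? |
|---|---|---|
| MCI | MoCA 24 or 25 | No, 22 is below the range |
| SCD | Normal on the tests that classify MCI | No, 22 is worse than an MCI score |
| Mild AD | NINCDS-ADRDA probable AD | No, there is no dementia |

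The same person with MoCA 24 would be admitted as MCI. The gap exists below each of the three ranges: below 13, below 19 and below 24.

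**3. Range or limit?** Nothing in the text supports reading the pairs as limits. The ADL item in the same list uses a less-than sign where a limit is meant. The other dashed figures in the section (MMSE 24–30 and 21–26) are true ranges.

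**4. Illustration of size.** Inputs are the earlier study's arm means and SDs. Assumptions: normality, a half-point continuity correction, at least 7 years of education, and arm values that resemble entry scores.

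- P(in 24–25) = Φ((25.5 − m)/s) − Φ((23.5 − m)/s)
- P(below 24) = Φ((23.5 − m)/s)

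| Source (m, s) | Below 24 | In 24–25 | Above 25 |
|---|---|---|---|
| Control (23.13, 1.68) | Φ(0.220) = 59% | Φ(1.411) − Φ(0.220) = 33% | 8% |
| Intervention (24.68, 1.84) | Φ(−0.641) = 26% | Φ(0.446) − Φ(−0.641) = 41% | 33% |

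For assumed MCI means of 21 to 24 and SDs of 1.68 to 3, 6–43% fall in the range and 38–93% below it.

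If 25 were an upper limit, the share of the control distribution meeting the item would rise from 33% to 92%. With 24 as the limit it would be 79%. These figures only show how much depends on the reading; they do not say which value is right.

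**5. MMSE overlap.** The ranges 24–30 and 21–26 share 24, 25 and 26, which is three of the six mild-AD scores.

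**The case against.** **The pairs may be a notation fault.** They could be boundary values written as ranges in a condensed article that rests on published MCI criteria, and nothing shows that the literal reading is used at screening. This is plausible, and it is a reason for restraint on severity. It does not remove the point: the article prints explicit numbers, and followed as printed they give a wrong result.

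**The illustration uses an uncertain distribution.** The values are arm means whose difference serves as the treatment effect, so they may be post-treatment scores. Neither time point nor education mix is given. This stands, and the shares are not estimates for this trial.

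**A reader might infer that about two thirds of MCI patients are rejected**, from 100% − 33% = 67% with the control figures. The documents do not support that. The 67% includes 8% above the range, who could count as normal and enter as SCD, and the other arm puts only 26% below.

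**A reader might also infer that some people fit both MCI and mild AD.** That does not follow from MMSE alone. Mild AD first needs probable AD, while MCI needs intact ADL, a MoCA score in range and no dementia. A double fit arises only if MMSE 24–30 is taken as the whole test of no dementia and the other MCI items are met. What stands is overlapping ranges with no order of precedence.

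**Mislabelling would not bias the arms.** Eligibility is settled before randomisation, and the article describes no stratification or analysis by diagnosis. This stands too.

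**Conclusion.** The gap is real on the plain wording. People without dementia and with intact ADL who score below their MoCA range have no entry category, although they are more impaired on that test than those admitted. On the illustrative assumptions above, 26–59% would fall below the 24–25 range and 33–41% inside it. The direction is certain; the size is not.

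The MMSE point is narrower: three shared scores and no stated precedence, softened by the separate requirement for probable AD.

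The harm is to eligibility, to diagnostic classification and to the generalisability of a claim across stages of AD. A reader might infer that the treatment comparison is compromised. It is not, because both arms are drawn from the same screened population. The passage should be corrected, but the fault does not threaten the validity of the trial.

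**What to change.** 1. The investigators reconcile the MCI item by restating each MoCA pair as the one-sided, education-specific limit intended. They confirm the value, and word the SCD item to match so that the two leave no gap.
2. State that dementia status is settled first by the NINCDS-ADRDA criteria, with MCI or SCD considered only in those without dementia. MMSE 24–26 alone then does not decide between MCI and mild AD.
3. Check the screening logs of people already enrolled or rejected against the corrected rule, and report any who would be classified differently.

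The cost is an amendment to one section and a review of existing logs. No procedure is added, and the sample size is unchanged.
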